### 8.2. WITHDRAWAL CRITERIA AND PLANNED ANALYSIS OF WITHDRAWALS AND ABANDONMENTS

Inclusion is defined as obtaining the subject's consent to participate in the study, regardless of whether eligibility is confirmed. Patients who have been included will discontinue their participation in the clinical trial if any of the following occur:

- Presence of a serious adverse event since inclusion that, in the opinion of the investigator or sponsor, may jeopardize patient safety or affect the results of the trial.
- Abnormal laboratory value(s), whenever in the opinion of the investigator and/or sponsor the safety of the patient is at risk or may interfere with the interpretation of the results of the study.
- Poor evolution or clinical conditions of the patient that prevent its continuity.
- Indication of prohibited medications or rescue therapies in case of poor wound evolution.
- Technical difficulties in the provision of the investigational drug. In this case, the patient may be re-evaluated when adequate production is possible. The patient will keep his or her assignment number in this case.
- When the patient does not cooperate or does not meet the requirements of the study.
- Withdrawal of consent or loss of follow-up by the patient.
- Pregnancy.

The patient has the right to discontinue the study at any time and any patient may be withdrawn from the study for any reason beneficial to their well-being. If, during the study, the patient's evolution makes it advisable to apply rescue therapies with proven efficacy, the patient will automatically leave the trial, and a failure of the therapy will be recorded in the course of the study will be treated within the guideline that the clinical experts and the health authorities decide.

For the purposes of the safety objective of the trial, safety follow-up of enrolled and withdrawn patients should be ensured throughout the duration of the clinical trial (12 months), to the extent possible. In any case, the date and reason why a subject discontinues participation in the clinical trial should be recorded in the Data Collection Notebook, and the sponsor should be notified immediately if the discontinuation is due to a Serious Adverse Event.

According to good clinical practice, all patients who leave the study prematurely will be given will attend according to the usual clinical practice. If withdrawal is due to a serious adverse event, patients will be monitored by the investigator or designee until appropriate completion, i.e., until the adverse event disappears or until it is determined to be permanent

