### 5.2. DESIGN

Multicenter, randomized, controlled, open-label proof-of-concept clinical trial.

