## 10. EVALUATION OF THE RESPONSE

### 10.1. MAIN VARIABLE

#### Feasibility

Defined as the possibility of completing the administration of the 4 doses of the investigational drug in at least 80% of patients randomized to the treatment group

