#### Safety:

Incidence of AE, SAE, AR, as well as SUAR, throughout the intervention period, as well as the 12 months after the end of treatment

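### Section 8.2 makes patients leave an open-label trial on results-related grounds, so later safety and outcome data can be lost selectively

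*Protocol*

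**What the plan says.** Section 8.2 of the protocol states that included patients "will discontinue their participation in the clinical trial if any of the following occur", and then lists the grounds. Two of them carry a results-related alternative:

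- **SAE:** an event since inclusion that, "in the opinion of the investigator or sponsor, may jeopardize patient safety or affect the results of the trial".
- **Laboratory:** an abnormal value, where the investigator and/or sponsor judge that "the safety of the patient is at risk or may interfere with the interpretation of the results of the study".

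The design in Section 5.2 is "Multicenter, randomized, controlled, open-label proof-of-concept clinical trial". The main safety variable in Section 10.1 is "Incidence of AE, SAE, AR, as well as SUAR, throughout the intervention period" and over the 12 months after treatment ends. The main feasibility variable is completion of four doses "in at least 80% of patients randomized to the treatment group".

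For patients who leave, Section 8.2 asks for safety follow-up "throughout the duration of the clinical trial (12 months), to the extent possible". Patients withdrawn for an SAE are followed until that event resolves or is judged permanent. The date and reason for leaving are recorded. Section 7 expects every patient to complete 12 months of follow-up after the last administration.

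**The concern.** In both criteria the word *or* makes the effect on the results sufficient by itself. The wording is compulsory and rests on opinion. For an SAE, one party's opinion is enough. It ends participation in the trial, not only treatment.

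An SAE always affects the results of a trial whose main safety variable counts SAEs, so the ground has no natural limit. The people who apply it know the arm and have seen the event. If it is used more readily in one arm than the other, the data missing afterwards depend on both arm and outcome. An analysis plan can say how to treat such gaps, but it cannot recover assessments that the protocol told sites to stop making.

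**Working it through.** The plan states no figure on this point, so there is none to reproduce. The check compares sections and then sizes what can be lost.

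**1. What survives a removal**

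- *The triggering SAE.* It must occur before the criterion can apply. Section 12.2 records events from consent, and Section 8.2 records the reason for leaving and follows the event to its end. If incidence is counted by patient, this patient already counts as having an AE and an SAE.
- *The feasibility denominator.* Section 10.1 uses patients randomized. A dosed patient removed before dose 4 remains in it as a non-completer. With 10 treated patients, 80% means at least 8 completers; 7 completers give 7/10 = 70%, a fail.

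**2. What later safety information is secured**

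| Section | Period after leaving |
|---|---|
| 8.2 | 12 months of safety follow-up, best effort |
| 8.2 | the triggering SAE only, until resolved or permanent |
| 12.2 | AEs and SAEs recorded until participation ends |
| 12.5.2 | SAEs reported up to 30 days after leaving |
| 10.1 | main safety variable: 12 months after treatment ends |

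Illustration, assuming that a patient leaves on the day of the last dose received and that 12 months is 365 days: firm SAE reporting covers 30/365 = 8% of the post-treatment window. The other 335 days rest on best effort. What is at risk is further events, later adverse reactions and unexpected serious reactions and, for patients removed on the laboratory ground, possibly a first SAE.

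**3. What later outcome data are secured**

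None. Section 8.2 asks only for safety follow-up of withdrawn patients. It does not keep ulcer measurement, Resvech, pain, CIVIQ-20 or exudate sampling.

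- *Exudate.* Section 10.2 has five sampling days (0, 7, 14, 21, 28). A patient who leaves after the day-7 sample contributes 2 of 5 and loses 3 of 5.
- *Healing at 12 weeks.* With 10 patients planned per arm (Section 5.3) and m of them leaving one arm before their status is known, the arm's healing proportion is undetermined over a width of m/10. For m = 1 that is 10 percentage points; for m = 2, 20 points. If the removals fall in one arm only, the difference between arms is undetermined by the same amount.

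**4. Reach of the laboratory ground**

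Section 7 lists blood tests at visit 1 and visit 14. Scheduled tests would therefore trigger it mainly before randomization or after day 84; earlier use needs an unscheduled test. Under Section 12.1 a laboratory deterioration is reported as an AE only if it is serious or is the reason for stopping the investigational product. The second route exists only in the experimental arm.

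**The case against.** The strongest reply is that the main results are protected. Much of it stands. A reader might infer three stronger points that the protocol does not support:

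- *Removal could turn a feasibility failure into a pass*, for example 7/8 = 87.5% in place of 7/10 = 70%. The denominator is patients randomized, so removing a dosed patient early can only lower feasibility. Section 5.5 also counts an AE that prevents the next dose as a failure. Section 8.3 appears to replace patients randomized but never dosed; its sentence is incomplete in the text, and nothing here rests on it.
- *Removal could delete the SAE from the safety comparison*, for example 3/10 = 30% becoming 1/8 = 12.5%. The event is recorded and followed, and the protocol nowhere says that withdrawn patients are dropped from analysis.
- *The sponsor's custody of the randomization list makes matters worse.* In an open-label trial the arm is known after assignment, whoever holds the list.

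Four further points have weight. Some best-effort qualifier on follow-up is unavoidable, because the same list includes loss to follow-up and withdrawn consent. The Data Security and Monitoring Committee (Section 1.16) advises on withdrawals, though only in doubtful cases. The patient-safety ground is also a matter of unblinded opinion and would often be available for an SAE, so deleting the results ground does not remove all discretion. Analysis sets belong to the analysis plan.

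None of this explains why an effect on the results should end a patient's participation, and none of it keeps the later outcome assessments.

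**Conclusion.** The point holds as a fault in what the protocol fixes. It requires patients to leave the trial on a results-related ground, applied with knowledge of arm and outcome. The exposure is selective loss of later safety information and of all later efficacy, quality-of-life and exudate data. It does not erase the triggering SAE or change the feasibility denominator.

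Each affected patient is one tenth of an arm. The sizes given assume the planned 10 per arm and removal before the assessment in question. How often the ground would be used is unknown, and could be never. The SAE criterion matters most; the laboratory criterion is narrower and its link to the main safety variable is indirect.

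**What to change.** 1. In the SAE criterion of Section 8.2, strike the alternative that follows the patient-safety ground in "in the opinion of the investigator or sponsor, may jeopardize patient safety or affect the results of the trial". In the laboratory criterion, strike "may interfere with the interpretation of the results of the study" and the *or* before it. Leave the patient-safety grounds unchanged.
2. Distinguish stopping study treatment from leaving the trial. Suggested wording: *A patient who stops study treatment and has not withdrawn consent continues, where he or she agrees, with the scheduled safety, ulcer, pain, quality-of-life and exudate assessments. The reasons for stopping treatment and for leaving the trial are recorded separately.*
3. Reconcile this with three statements: the lead-in to Section 8.2, which ends participation; its later paragraph, under which a patient given rescue therapy leaves the trial automatically; and Section 7, which expects 12 months of follow-up for all. Align the recording and reporting periods in Sections 12.2 and 12.5.2 with the 12-month window of the main safety variable.

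Analysis sets can stay with the analysis plan. The cost is an amendment to a few passages and some additional visits by patients who have stopped treatment.

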### 5.3. SAMPLE SIZE

Twenty patients with VUs, who meet all inclusion criteria and none exclusion criteria, will be included and will be randomized 1:1 to two intervention arms: experimental and control (10 patients treatment group/10 patients control group).

The 10 patients in the experimental arm will receive 4 doses of the investigational drug: adult mesenchymal stem cells from adipose tissue expanded in the biological matrix of fibrin-hyaluronic acid on the base or wound bed, while the 10 patients in the control group will be treated with conventional therapy.

This is a phase I/II clinical trial, proof of concept, of which there are no previous studies, so no mathematical calculation of the sample size has been carried out.

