### 10.2. SECONDARY VARIABLES

Effectiveness:

The answer will be analysed through clinical and biological parameters

Clinical variables:

- Percentage of patients who achieve complete healing at 12 weeks of follow-up (complete epithelialization maintained for 2 weeks) when comparing control group versus treatment.
- Time elapsed (days) to wound closure, measured from the start of treatment to the absence of continuity solution (when the wound bed is completely re-epithelialized and with new tissue) when comparing control group versus treatment.
- Percentage of patients who presented better in the total score and by Resvech 2.0 scale (size of injury, depth of affected tissues, borders, type of tissue in the wound bed, exudate, and infection · inflammation) with respect to baseline and when comparing control group versus treatment.
- Percentage reduction in wound extension (relative area, measure, graded rule) with respect to baseline visit and when comparing the control group versus the experimental group.
- Percentage of patients who have a decrease in the score of the AVS pain scale with respect to the baseline visit when comparing the control group versus the experimental group.
- Percentage of patients who perceive better quality of life according to the score obtained in the CIVIQ20 throughout the treatment/follow-up with respect to the baseline visit and when comparing both groups.

Biological variables:

- Evolution of the pattern of cytokines and growth factors obtained from ulcer exudate samples at day 0, +7, +14, +21 and +28 when comparing both groups and their relationship with ulcer healing.

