## 11. STATISTICAL ANALYSIS

The statistical analysis will be carried out by an independent biostatistician under the supervision of the project's Principal Investigator. All continuous variables will be described using standardized statistical measurements. The categorical variables will be summarized in frequency tables. For descriptive analyses, absolute or relative frequencies will be used in the case of relative variables. The

quantitative variables, depending on whether they follow a normal distribution (Saphiro-Wilk ( $n < 50$ )), will be shown as  $m \pm SD$  (mean and standard deviation) and range (minimum and maximum) or P50 [P25-P75]

(median, interquartile range). To compare the different variables in the two groups, the Pearson Chi-square test or the exact Fisher test will be applied in the case of qualitative variables, while , for quantitative variables, the ANOVA and post hoc tests or the Kruskal-Wallis H and Mann-Whitney U tests will be used, always applying the Bonferroni correction ( $\alpha/\text{number of possible comparisons}$ ). Values with  $p < 0.05$  will be considered statistically significant.

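### Patients who leave for poor wound evolution or rescue keep only safety follow-up, so later efficacy data, above all wound area, are missing because of the outcome itself

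*Protocol*

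**What the plan says.** Protocol section 8.2 lists the reasons for ending participation. Two depend on how the wound is doing: "Poor evolution or clinical conditions of the patient that prevent its continuity" and "Indication of prohibited medications or rescue therapies in case of poor wound evolution". For rescue the section adds that "the patient will automatically leave the trial, and a failure of the therapy will be recorded".

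What continues afterwards is tied to one purpose: "For the purposes of the safety objective of the trial, safety follow-up of enrolled and withdrawn patients should be ensured", for 12 months and as far as possible. Patients who leave early are otherwise cared for under usual practice. No section keeps area, RESVECH, VAS or CIVIQ-20 assessments going after withdrawal.

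Section 10.2 compares the arms on complete healing at 12 weeks, time to closure, RESVECH, area, pain and quality of life. The area variable is "Percentage reduction in wound extension (relative area, measure, graded rule) with respect to baseline visit". RESVECH, pain and quality of life are each defined as a percentage of patients who improve. Section 10.2 does not say how a recorded therapy failure enters any of these. Section 5.5 defines non-response through adverse events only.

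On size, patients "will be randomized 1:1 to two intervention arms: experimental and control (10 patients treatment group/10 patients control group"), and "no mathematical calculation of the sample size has been carried out".

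**The concern.** Secondary objectives 2, 4 and 5 (section 4.2) compare wound evolution, pain and quality of life between arms. Under section 8.2, poor wound evolution is also a reason for measurement to stop. Whether a later value exists then depends on the outcome being compared. If exits are more frequent in one arm, that arm's remaining patients look better than the arm as randomised.

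The trial is open-label (section 5.2) and section 8.2 gives no measurable threshold for poor evolution, so the timing of exit could differ by arm. Nothing shows that it will.

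A statistical analysis plan can choose an analysis set or an imputation rule. It cannot recover measurements that the protocol never asked for, so this has to be settled in the protocol. At stake is the credibility of the secondary efficacy comparisons, which a proof-of-concept trial would use to plan the next study.

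**Working it through.** The protocol gives no effect size, SD, dropout rate or power, so there is no stated figure to reproduce. The check has three parts.

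**1. What a recorded failure can and cannot supply**

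| Variable (section 10.2) | Form | After exit for rescue |
|---|---|---|
| Complete healing at 12 weeks | percentage of patients | the failure can count as not healed |
| RESVECH | percentage improved | the failure can count as non-response; not stated |
| VAS, CIVIQ-20 | percentage improved | could count as non-response, but a wound failure does not show that pain or quality of life failed to improve |
| Percentage area reduction | continuous | no natural failure value |

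**2. Area: effect of losing the worst patients**

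Input from the protocol: 10 per arm (section 5.3) and significance at p < 0.05 (section 11; sidedness not stated, taken as two-sided). Assumed: week-12 area reduction is normal with mean 60% and SD 30, 40 or 50 in both arms, so there is no true effect; the k worst patients in an arm leave; only completers are compared, by t-test. The normal model is crude, since a reduction cannot exceed 100%.

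If the k removed patients have mean m_w and the whole arm has mean m, the retained mean exceeds m by k(m − m_w)/(10 − k). Simulated differences, experimental minus control, in percentage points:

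| Worst patients lost, control / experimental | SD 30 | SD 40 | SD 50 | False-positive rate |
|---|---|---|---|---|
| 0 / 0 | 0.1 | −0.1 | 0.1 | about 5% |
| 1 / 0 | −5.1 | −6.9 | −8.6 | about 7.5% |
| 2 / 0 | −9.5 | −12.7 | −15.9 | about 11% |
| 3 / 0 | −13.7 | −18.1 | −22.8 | about 17% |
| 4 / 1 | −12.7 | −17.0 | −21.2 | 18 to 19% |
| 2 / 2 | −0.1 | 0.0 | 0.0 | about 9% |

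A negative figure favours control, the arm that lost more failures. With the arms exchanged, the sign reverses.

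Check against the formula for 2 / 0 at SD 40: 12.7 = 2 × gap / 8, so gap = 12.7 × 8 / 2 = 50.8 points. The two worst of ten lie on average 50.8 / 40 = 1.27 SD below the arm mean, which is plausible. The shift scales with the SD: one loss costs 5.1 / 30 = 6.9 / 40 = 8.6 / 50 = 0.17 SD.

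In the 2 / 2 case the bias cancels, but at SD 40 both arm means are about 13 points too high (about 73 against 60).

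**3. Percentages of patients: the denominator decides**

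Take 5 of 10 improved (assumed). If 1, 2, 3 or 4 non-improvers drop out of the denominator, the result is 5/9 = 56%, 5/8 = 63%, 5/7 = 71% or 5/6 = 83%. If they are kept and counted as failures, it stays at 5/10 = 50%.

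**The case against.** A reader might infer that the secondary endpoints will be compared only among ulcers that are doing well, or that the trial cannot answer objectives 2, 4 and 5. The document does not support either reading:

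- No section prescribes a completers-only comparison, and the analysis set and missing-data rule may stand in an analysis plan that is not shown.
- Poor evolution ends participation only where it prevents continuity. Section 7 keeps unhealed ulcers of patients still in the trial in weekly efficacy follow-up, so slow or enlarging ulcers without rescue stay in.
- Values from before the exit exist and can be used.
- Three of the four variables at issue are percentages of patients, where a recorded failure can count as non-response.
- The exit decision is not simply left to the investigator. Section 1.16 has the DSMC advise on doubtful withdrawals.

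All of this stands and limits the point. It does not remove it, because none of these provisions produces an area, pain or quality-of-life value after exit.

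A second objection is that values taken after rescue partly reflect the rescue and do not show what would have happened without it. That is also correct. It bears on how such values are read, not on whether to collect them: with the values and the failure date, both a treatment-policy analysis and a failure-based analysis are possible. Without the values, the first is not.

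Finally, all affected variables are secondary in a small proof-of-concept trial. That limits the severity.

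**Conclusion.** The point holds in a limited form. Following section 8.2 as written makes efficacy data after exit for poor evolution or rescue missing not at random. Percentage area reduction is hit hardest; RESVECH, VAS and CIVIQ-20 are affected to a lesser degree. The result is a risk of bias in secondary comparisons, not their loss.

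The 5 to 23 point shift for 1 to 3 unequal exits rests on assumed means and SDs, on the worst patients being exactly those who leave, and on a completers-only analysis. It shows how sensitive 10 per arm is and does not predict the trial's result. Feasibility and safety are little affected, and safety follow-up is kept. An amendment is worthwhile, but the primary objectives do not depend on it. Nothing here judges when rescue should be given.

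**What to change.** In section 8.2, leave the decision on rescue as it is, and separate stopping study treatment or starting rescue from leaving the trial. Then state that:

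- unless consent is withdrawn, these patients keep the area, RESVECH, VAS and CIVIQ-20 assessments already scheduled up to visit 14 (day 84);
- the values are analysed in the randomised arm, with the failure date shown;
- a recorded therapy failure counts as not healed, and as non-response in the RESVECH responder variable;
- the area comparison is shown both with post-rescue values and with rescued patients treated as failures, for example ranked worst.

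Cost: amendment wording and a failure-date field. The date and reason for discontinuation are already recorded, the visits are already scheduled for other patients, and withdrawn patients are already to be followed for safety. Some of them will need assessment visits on top of safety contact. The scheduled follow-up visits include Annex 4 wound treatment, whereas patients who have left receive usual care, so the protocol should define these as assessment visits. Post-rescue values will partly reflect the rescue, which is why the two area analyses belong side by side.
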